## Abstract

**Background:**

Lung cancer is the leading cause of cancer-related death globally. Physical activity and exercise provide unequivocal benefits to those living with and beyond lung cancer. However, few of those living with and beyond cancer meet the national physical activity guidelines. Various barriers exist for this population’s engagement in physical activity and exercise, such as the lack of knowledge and lack of tailored information, little access to exercise specialists, fatigue, and mobility challenges. Digitally delivered programmes have the potential to address several of these barriers, with techniques like “computer-tailoring” available to enable the delivery of tailored content at a time and place that is convenient. However, evaluation of such programmes is needed prior to implementation. This protocol describes a single group study that will examine the feasibility and acceptability of an online tool (ExerciseGuide UK) that provides those living with and beyond lung cancer web-based computer-tailored physical activity prescription and modules underpinned by behaviour change theories.

**Methods:**

Thirty-five individuals diagnosed with lung cancer, or cancer affecting the lung (e.g. pleural mesothelioma), will be recruited into a single-intervention arm. The platform will provide tailored resources and a personalised physical activity programme using IF-THEN algorithms. Exercise prescription will be tailored on factors such as self-reported specific pain location, exercise history, and current physical fitness. In addition, modules grounded in behaviour change will supplement the physical activity programme and will focus on topics such as exercise benefits, safety, goal setting, and tracking. The primary outcome will be assessed using pre-established criteria on feasibility and mixed-methods approach for acceptability.

Secondary outcomes will explore changes in the physical activity, quality of life, anxiety, and depression.

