## Methods

### Study design

This study is a single-group feasibility study. The participants will complete an 8-week web-based computer-tailored physical activity intervention with personalised educational resources. Mixed-methods analyses will be employed with primary outcomes exploring the feasibility and acceptability of the web-based platform. Secondary outcomes examining quality of life, anxiety, and depression will be collected via questionnaires. Physical activity and exercise will be collected weekly via tracking modules, wherein participants can self-report physical activities and exercises completed and any concerns. Fifteen participants will be invited to participate in post-study interviews will be conducted. Interviews will continue if not saturated.

The study has been registered on the ClinicalTrails.gov website [43] (ID: NCT05121259)*,* and ethical clearance was obtained by the Health Research Authority (approval: 21/SC/0174). The reporting of the study protocol adheres to the Standard Protocol Items: Recommendations for Interventional Trials (SPIRIT) guidelines [44]. A participant timeline is presented following the SPIRT guidance in Table 1.

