##### Aerobic exercise

Aerobic exercise will be based on their current activity levels. The aerobic physical activity information provided will help participants with suggestions for increasing activity and meeting the physical activity guidelines (if appropriate) for those living with and beyond cancer [13, 61–63]. In addition, the information provided (see Fig. 10) will give examples of exercises with a collapsible drop-down option detailing supplementary information regarding aerobic recommendations and considerations covering the FITT (frequency, intensity, time, and type) principle in detail. Aerobic exercise information is provided based on the participants’ current self-reported aerobic exercise. Using the government guidance of 150 moderate–75 vigorous minutes per week, the participants recorded their current level of aerobic activity. ExerciseGuide UK then illustrated how the participant can increase their aerobic activities in smaller bouts of aerobic activity to reach the recommended guidance [13].

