##### Tracking

An online tracking module has been created to support participants to track their physical activity and general thoughts. The tracking module will provide a mix of open and closed questions regarding aerobic and resistance exercise, health-related fitness, motivation and habits, and general comments. Additionally, the tracking module will provide tailored feedback. This module will be released weekly, though a selection of data (motivation and health status) will be pulled through to subsequent weeks for graphical features (e.g. enablers and health/symptom check-in). Visual aids such as responsive graphs can present past and present data to show progress. The participants will be sent an email reminder upon the release of the tracking module.

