#### Health-related outcomes

Health-related outcomes will be collected at baseline upon registration to the website and immediately following the completion of week 8. The health-related outcomes being assessed pre- and post-study will be the quality of life, anxiety, and depression. Health-related quality of life will be explored via the 30-item European Organisation for Research and Treatment of Cancer Quality of Life Questionnaire-validated questionnaire (EORTC QLQ-C30; version three) [75]. The quality of life domains are divided into multi-item subscales, functional (e.g. physical, role, cognitive, emotional, and social), symptom scales (e.g. fatigue, pain, nausea/vomiting, and dyspnoea), financial hardship, and global health status.

Anxiety and depression will be measured using the Hospital Anxiety Depression Scale [76]. The Hospital Anxiety Depression Scale will measure anxiety and depression using a 14-item scale (seven items for depression and seven items for anxiety). The Hospital Anxiety Depression Scale has been illustrated to show an excellent screening of those with and without clinical symptoms of depression and anxiety to longer questionnaires (MADRS-S and STAI-S) using web-based platforms for those living with and beyond cancer [77].

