##### Quantitative data

The quantitative data will be exported to SPSS version 26 (IBM, Chicago, IL, USA) for analysis. Descriptive statistics of the sample and each study measure. Data obtained from the EORTC-QLQ-30 and Hospital Anxiety Depression Scale will be analysed using a paired *t* test (non-parametric, Wilcoxon test). The weekly self-report tracking module will examine adherence to the exercise prescription. Changes in attitudes to physical activity, confidence, and burden will explored post-intervention.

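### Change in physical activity is a secondary outcome in the abstract, but the text designates no matched baseline and week-8 activity measure and no change analysis

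*Protocol article*

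**What the plan says.** The abstract (Methods) sets the secondary aim: "Secondary outcomes will explore changes in the physical activity, quality of life, anxiety, and depression".

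The body of the article treats activity differently from the other three outcomes:

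- Study design names the secondary outcomes without activity: "Secondary outcomes examining quality of life, anxiety, and depression will be collected via questionnaires". It then deals with activity separately: "Physical activity and exercise will be collected weekly via tracking modules, wherein participants can self-report physical activities and exercises completed and any concerns".
- Health-related outcomes fixes two assessment times, registration and the end of week 8, and lists what is assessed at them: "The health-related outcomes being assessed pre- and post-study will be the quality of life, anxiety, and depression".
- Tracking says of the tracker: "This module will be released weekly". It also says that the module returns tailored feedback. Table 2 lists it among the intervention modules, with self-regulation as one of its mechanisms of action.
- Quantitative data gives a paired test to the EORTC questionnaire and the Hospital Anxiety Depression Scale. The role it gives the tracking data is adherence to the prescription.
- Aerobic exercise describes a starting value used for tailoring: "the participants recorded their current level of aerobic activity". The Fig. 10 caption shows its form, minutes per week, with 50 as the example.

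Quantitative data also contains a sentence on other constructs: "Changes in attitudes to physical activity, confidence, and burden will explored post-intervention".

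**The concern.** A change outcome needs the same quantity measured in the same way at two times, and an analysis that uses both. The abstract promises this for physical activity, but the body does not say which two measurements make up the change.

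Followed as written, the plan gives the analyst a weekly self-report made during the programme, inside a module designed to influence the behaviour it records. A trend across those weeks describes how logged activity moved while people were using the programme. It is not a contrast with their activity before they started, and it rests on those who chose to log.

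The stakes are moderate. The outcome is secondary, and no feasibility or acceptability criterion depends on it. But it is the behaviour the intervention is meant to alter, and the Conclusion says the authors plan a later comparison of a digital activity tool with standard care. A usable before-and-after activity measure is a natural thing to pilot for that.

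**Working it through.** There is no arithmetic to reproduce. The article attaches no figure to this outcome, and its sample size of 35 does not come from a formal calculation. The check sets each change outcome in the abstract against the measures and analysis sections.

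| Outcome in the abstract | Called a secondary outcome in Study design | In the pre/post set (Health-related outcomes) | Named instrument | Paired analysis (Quantitative data) |
|---|---|---|---|---|
| Quality of life | Yes | Yes | EORTC QLQ-C30 | Yes |
| Anxiety | Yes | Yes | HADS | Yes |
| Depression | Yes | Yes | HADS | Yes |
| Physical activity | No, described separately | No | Weekly tracker only | No; tracker used for adherence |

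Three of the four rows are complete. The fourth is not.

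The next question is whether other data described in the text could supply the missing pair.

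1. **Tracker against tracker.** "Physical activity and exercise will be collected weekly via tracking modules", and the module is released week by week on the 8-week platform. The text states no administration before the programme. That the first entry falls after the start is a reasonable inference, but the text gives no first release date.
2. **Tailoring question against tracker.** A starting value for aerobic activity exists in minutes per week. It is not designated as an outcome baseline, and nothing says that the tracker asks the same question. The Resistance exercise section says that tailoring also uses current activity and exercise levels, but does not describe the form of those answers. Subtracting one source from the other could therefore mix two questions, and would be limited to participants with a tracker entry.
3. **Tailoring question against a repeat at week 8.** This would be like for like, but the text does not say that the question is asked again.

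The third pairing is the clean one. Half of it, the starting answer, is already collected.

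The sentence on attitudes, confidence and burden is a smaller matter. It speaks of changes but places the assessment after the intervention, and the Measures section describes no baseline for these items. If they are asked once, they measure change as participants perceive it.

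**The case against.** The strongest reply is that this is under-specification in a condensed article about a feasibility study. A starting aerobic value is recorded, the tracker supplies later values, and the abstract says only that changes will be explored. Table 1, captioned as covering enrolment, baseline, intervention and assessments, and Fig. 4, which gives the module release timings, are not available here. Either might show a baseline activity entry. A confidence interval for the change is the kind of detail an analysis plan would hold.

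Much of this stands. A reader might infer that activity is not measured at all before the programme, or that its change cannot be estimated. The documents do not support either reading. Aerobic minutes are self-reported for tailoring, so a rough contrast with later entries is possible, as is a trend across tracked weeks. Nor can it be taken as fact that tracking begins only once the intervention is under way. The size of any distortion cannot be given either, because the article reports no activity data beyond one example screen.

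The attitudes sentence can also be read fairly as perceived change asked once, which is a legitimate approach. The qualitative section supports this, since the interviews are to explore behaviour and attitude change.

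What the reply does not remove is the conflict within the text. The list under Health-related outcomes names what is assessed before and after, and activity is not in it. The analysis section gives the tracking data a different purpose. These statements disagree with the abstract, so more than detail is missing. An analysis plan could define a contrast from the data collected, but it could not create a matching week-8 answer that nobody was asked to give.

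**Conclusion.** The point holds as an inconsistency between the stated outcome and its measurement. Change in physical activity is named as a secondary outcome, but the text designates no matched baseline and week-8 measure and no change analysis for it. One of the four change outcomes in the abstract is affected. The primary feasibility and acceptability criteria are not.

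The conclusion is limited to what the text specifies. It assumes that Table 1, Fig. 4 and any fuller protocol do not already schedule a repeated activity question. If they do, the article only needs to say so. It does not claim that no starting value exists or that no change of any kind could be computed. This is an inexpensive improvement worth making, not a flaw that undermines the study.

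**What to change.** - Keep the activity answers already collected for tailoring, and designate them in the protocol as the outcome baseline.
- Repeat the identical questions in the existing week-8 questionnaire, put to everyone enrolled and not only to those who use the tracker.
- Define the outcome as week 8 minus baseline and report it with a 95% CI. Keep the tracking data for adherence.
- If this is not wanted, remove change in physical activity from the secondary outcomes in the abstract, so that it agrees with Study design, Health-related outcomes and Quantitative data.
- If the attitudes, confidence and burden items are asked only once after the intervention, describe them as participant-perceived change.

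The cost is two or three extra items in a survey that participants already complete, plus changes of wording. For those already registered, the stored tailoring answers may serve as the baseline.

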**Discussion:**

This manuscript describes the protocol for a study examining the feasibility and acceptability of a web-based computer-tailored physical activity intervention for those living with and beyond lung cancer. The publication of this protocol aims to increase the transparency of the methods, report pre-determined criteria, and aid replication of the study and associated materials. If feasible and acceptable, this intervention will inform future studies of digital-based interventions.

**Trail registration:**

ClinicalTrails.gov, NCT05121259. Registered on November 16, 2021.

**Supplementary Information:**

The online version contains supplementary material available at 10.1186/s40814-022-01129-6.

## Introduction

Lung cancer is the second most diagnosed malignancy and the leading cause of cancer-related death globally [1]. Those living with and beyond lung cancer (LWBLC) may experience several curative treatment procedures, including chemotherapy, radiotherapy, immunotherapy, and surgery. Though potentially lifesaving, these treatments can lead to and exacerbate a number of long-lasting symptoms such as fatigue, loss of cardiorespiratory fitness, pain, and breathlessness [2–6]. Often, those LWBLC report feelings of low mood and depression, as they are forced [2–4] to accept the changes to their life caused by a diagnosis of cancer [7].

Physical activity and exercise are often used interchangeably within literature, though they are not synonymous [8]. Physical activity is defined as any bodily movement caused by the skeletal muscle which results in energy expenditure [9, 10]. Exercise is a subset of physical wherein an individual is in physical activity in a purposive, structured, and repetitive manner, with the intention of improving or maintaining one or more components of physical fitness [9, 11]. Engaging in a regular physical activity and exercise, in particular, is a recommended strategy for improving health and quality of life among cancer patients [12]. The American College of Sports Medicine (ACSM) has highlighted the benefits of physical activity that can elicit for those living with and beyond cancer [13]. Despite the increase in research in this area, the most robust evidence base is still primarily drawn from early-stage breast and prostate cancer survivors.

Nevertheless, amongst those LWBLC, physical activity and exercise has demonstrated to have several positive biological and physiological effects, such as reducing fatigue, anxiety, and depression while increasing muscle strength, increasing quality of life, and mitigating treatment side effects [14]. Furthermore, evidence supports the guidance for those living with and beyond cancer, including those LWBLC, to increase their physical activity post-diagnosis to increase survival outcomes [15, 16]. Cancer cachexia is a multifaceted syndrome with progressive loss of the skeletal muscle [17] and occurs in 20% of early stage lung cancer [18], 40% metastatic non-small cell lung cancer [19], and up to 69% of advanced lung cancer [20]. Increasing muscle strength and muscle mass may be beneficial in reducing the rate of muscular wasting and cancer cachexia [21]. However, the majority of this population worldwide does not meet the physical activity guidelines [22–25]. There are a multitude of reasons for this. In addition to common barriers to physical activity such as lack of time, access to facilities, and motivation, people LWBLC have disease-specific barriers. These can include fear of breathlessness, fatigue, pain, lack of knowledge about activity, symptom burdens, mood, and fear [14, 26]. People LWBLC have also reported a lack of physical activity recommendations and advice from oncology clinicians [27]. There is a clear need to explore and develop new supportive and survivorship care methods to better support patients. A study by Lin and colleagues (2013) interviewed people LWBLC and found that 70.4% of patients showed an interest in physical activity programmes. Furthermore, 69.1% of patients LWBLC reported they had the ability to participate in physical activity programmes [28].

A meta-analysis of patient-level data reported that supervised exercise programmes yield a greater quality of life and physical functioning improvements than unsupervised programmes [29], though both supervised and unsupervised exercise programmes were better than usual care control groups. Supervised programmes are thought to have greater efficacy owing in part to greater ability to provide personalised exercise programming and support. However, digital technology has been a promising method of providing personalised supportive care over a distance [30]. Digital health technology (also known as eHealth) has existed in health research for several years, though there has been an exponential growth throughout the coronavirus 19 (COVID-19) pandemic. A recent review exploring the feasibility of exercise interventions delivered via telehealth for those living with and beyond cancer highlighted that 6.8% of studies explored lung cancer, whereas breast cancer represented 62% [31]. Thus, it is critical that suitable digital technology is created to support those LWBLC, given the majority of research focuses on those living with and beyond breast and prostate cancer.

Those LWBLC tend to be older individuals (≥ 65y); within the UK, 44% of new diagnoses of lung cancer are those ≥75 years [32]. Given the typical elderly nature of those LWBLC, web-based platforms may increase usability with larger fonts, images, videos, and designs that require less precise mouse manoeuvrability as compared to printed materials or smartphone apps [33]. Additionally, web-based platforms have the capability to deliver personal advice (a.k.a. computer-tailored programmes), educational resources, behaviour change advice, and self-and symptom-monitoring. Notably, these programmes and resources can provide a high-quality and personalised content, promote remote access, minimise travel, and allow the user to maintain a sense of anonymity while maintaining low overall cost [34–36]. Given this ability, it is possible to build on the foundations of movements such as exercise is a medicine and lifestyle medicine [37, 38].

Those LWBLC are more likely to become seriously ill if contracting the COVID-19 virus due to their older age or undergoing chemotherapy and/or radiotherapy, which suppresses their immune system [31]. Given the high symptom burden and the complexity of the treatment-related side effects, such as immunosuppression with chemotherapy agents, there must be an alternative to the typical face-to-face supervised approach. Digital health exercise interventions have previously demonstrated feasibility/acceptability for those living with and beyond breast, gynaecological, multiple myeloma, myelodysplastic syndrome, lymphoma, Hodgkin lymphoma, Leukaemia, non-Hodgkin lymphoma, endometrial, prostate, and metastatic prostate cancer [31, 34, 39]. However, our previously published review shows that online supportive care is in its infancy for those LWBLC, particularly for physical activity focused online supportive care [40]. Our study aims to conduct a feasibility pilot study of a computer-tailored web-based platform, ExerciseGuide UK, which will add to the limited available evidence for those LWBLC. This protocol details the steps taken to adapt an existing platform that has been used for those with a history of breast cancer [41, 42] and metastatic prostate cancer [39] for those LWBLC and describes the methods of the single-group feasibility study. Publication of this protocol intends to increase the transparency of the steps taken to adapt and develop this intervention and develop a more comprehensive understanding of scientific rigour and results.

## Methods

### Study design

This study is a single-group feasibility study. The participants will complete an 8-week web-based computer-tailored physical activity intervention with personalised educational resources. Mixed-methods analyses will be employed with primary outcomes exploring the feasibility and acceptability of the web-based platform. Secondary outcomes examining quality of life, anxiety, and depression will be collected via questionnaires. Physical activity and exercise will be collected weekly via tracking modules, wherein participants can self-report physical activities and exercises completed and any concerns. Fifteen participants will be invited to participate in post-study interviews will be conducted. Interviews will continue if not saturated.

The study has been registered on the ClinicalTrails.gov website [43] (ID: NCT05121259)*,* and ethical clearance was obtained by the Health Research Authority (approval: 21/SC/0174). The reporting of the study protocol adheres to the Standard Protocol Items: Recommendations for Interventional Trials (SPIRIT) guidelines [44]. A participant timeline is presented following the SPIRT guidance in Table 1.

